# *Description of current infrastructure and resources available for the study*

The MRC’s Field Station in Farafenni has carried out a series of trials since 1998 to determine the safety, efficacy/effectiveness, gametocyte prevalence, density and infectivity to mosquitoes of treatment of uncomplicated malaria with various combinations of antimalarials. A stable colony of A. gambiae mosquitoes has been established in the insectary at the Field Station and these will serve as the source of adult mosquitoes for the feeding experiments. In 2003 we completed a large trial of the effectiveness of three alternative drug combinations for treatment of acute uncomplicated malaria in the same three centres. We propose to adopt a similar design and recruit in the same centres in 2004 for the Lapdap trial, using the same trained staff and equipment. Molecular methods for drug resistance typing are being established in the malaria laboratories in Farafenni and Fajara. G6PD genotyping is established in [name] laboratory in Fajara.

**B4 Details of study design and investigations**

This section is designed to give the Committees sufficient information to see clearly and quickly the scientific and ethical aspects of the study design. Some parts will not be relevant to all studies. For studies at MRC Laboratories, the please discuss data management arrangements with the Head of Computing. For clinical studies, please discuss the clinical service commitments with the Clinical Director. If you have questionnaires or consent forms prepared, please attach these to the application.

1. **What type of study design is proposed (eg case control, prospective cohort, randomised controlled trial, etc)**

Randomised controlled trial

1. **What is the proposed size of the study (this may relate to patients, cases, controls, survey subjects, laboratory samples etc, as appropriate).**

We require at least 1180 patients to be randomized, this allows for 10% loss to follow up.

1. **Please describe the statistical considerations and sample size calculations involved in determining the size of the study.** (If you do not have access to statistical advice, please consult the MRC Laboratories Statistics Department.)

The sample size is based mainly on the primary endpoint but takes account of a number of other objectives as well. We wish to be able to detect clinically important differences in efficacy, but in the case that both treatments appear similar in efficacy, we will want to be able to rule out the possibility that one of the treatments may be worse, so it is important that the difference in treatment failure rates is estimated with sufficient precision (non-inferiority). We wish to demonstrate that the new combinations are at least as good as each other within a margin of 3%. To have at least 80% power for this, using the method of Farrington and Manning and a significance level of 0.025. The trial will be part of a multi-centre study to be sponsored by WHO. We will pool data from all participating countries for analysis of impact of G-6-PD deficiency on anaemia

1. **For studies involving human subjects. How and where will the study subjects (cases, controls, etc) be selected? Has it been confirmed that they are not already involved in other studies?**

The study subjects will be children presenting to Farafenni MCH clinic, and Njaba Kunda and Brikama Health Centres with a febrile illness and a blood film confirms they have significant parasitaemia. There is ongoing demographic surveillance system in the Farafenni area but this does not preclude enrolment into a clinical trial.

1. **What inclusion/exclusion criteria will be applied?**

The following will be included in the study:

- Children aged 0.5-10 years of age presenting with symptoms of acute malaria infection
- Axillary temperature of  37.5C
- Positive blood smear with monoinfection with *P. falciparum*
- Parasite density of 2000-200 000 parasites/L of blood
- Packed cell volume (PCV) 20%
- Free and informed consent of their parents or legal guardians

The following children will be excluded:

- Those with symptoms and signs of severe and complicated malaria
- Severe malnutrition, defined as 3SD below weight for height
- Clinically evident concomitant disease
- History of allergy to the study medications
- Those with a potential problem with follow-up, e.g. if a trip outside the study area is planned before the end of the follow-up period.

1. **What samples, if any, will be taken and what investigations will be conducted?**

- Finger-prick samples on days 0, 7, 14 and 28 and on any day that a study patient returns sick to hospital for thick films for malaria parasite detection and filter paper blood spots for molecular typing and packed cell volume (PCV)/haemoglobin determination.
- 2-3 mL blood by venepuncture on day 7 (MRC Camp in Farafenni only) from consenting gametocyte positive patients for drug level determination and membrane feeding of mosquitoes
- Alcohol-fixed oocysts from infected mosquito guts for genotyping

1. **Will treatment be given? YES  NO **

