From the finger-prick blood samples collected on filter paper at screening and from samples taken from parasitological treatment failures, 10-20μl aliquots will be tested using nested PCR on extracted DNA to detect point mutations in genes associated with resistance to sulfadoxine-pyrimethamine DHFR (codons 51, 59, 108) and DHPS (codons 437, 540), in order to examine their possible association with Lapdap treatment failure. In addition, if a child has a second episode of parasitaemia, samples from the first and second episode will be assayed for the three sequence families of MSP1 block 2 repeat region and the two sequence families of the MSP2 repeat region, to distinguish recrudescence from reinfection. Since patients with glucose-6-phosphate dehydrogenase (G6PD) A- deficiency are more susceptible to the haemolytic effects of the dapsone component of Lapdap, in this trial we will determine the G6PD genotype using an ARMS PCR technique. Retrospectively, we will screen for the two A- associated mutations, an A to G transition at position 376, encoding the B (normal) to A change (Asn126Asp), and a G to A transition at position 202, encoding the specific A- change (Val68Met), and we will also measure enzymatic activity, in order to evaluate the extent to which the risk associated with the use of the drug in settings without G6PD screening might outweigh the benefits to malaria treatment.

In addition we will measure concentrations of drug components in a sample of day 0 samples and in day 7 samples, using the HPLC method at LSHTM, as a verification of compliance with treatment. An economic component to the studies will be incorporated to assess provider costs as well as social costs associated with treatment and with treatment failure. Qualitative research techniques will be used to investigate mothers’ perceptions of antimalarial treatment and operational issues.

*Endpoints, sample size, randomization, and data management*

The primary endpoint will be clinical and parasitological cure by day 28. Secondary endpoints include the incidence of clinical anaemia at any time during the 28 day follow up, defined as clinical signs of anaemia and Hb that has fallen by 2g/dl or more from the day0 measurement; and change in Hb from day0 to day 28; and percentage transmission on day 7 and day 14 after treatment.

The trial will not be blinded, but the randomization procedure will ensure concealment of the allocation sequence. Databases will be designed in Access.

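### The 80% power is attached to a mutual claim with no reference arm, but the cited method gives power for one direction only, and the text does not say which is meant

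*Protocol*

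**What the plan says.** The primary endpoint is binary. Under Study design and methods (B3): "The primary endpoint will be clinical and parasitological cure by day 28".

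The sample size is in section B4. It first says that, should the drugs look similar, "we will want to be able to rule out the possibility that one of the treatments may be worse", and it puts the label non-inferiority in brackets after asking for a precise estimate of the difference in failure rates. It then states the aim: "We wish to demonstrate that the new combinations are at least as good as each other within a margin of 3"%. The next sentence attaches the power to that aim: "To have at least 80% power for this, using the method of Farrington and Manning and a significance level of 0.025". The size is given just before: "We require at least 1180 patients to be randomized, this allows for 10% loss to follow up".

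B4 gives no expected failure rate, no reference arm, no allocation ratio and no assumed true difference. The one day-28 cure figure quoted for a regimen under study is in B1 Background: 97% for six-dose co-artemether in Thailand. It is not offered as a planning value.

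**The concern.** The aim has two parts: Lapdap is not worse than co-artemether by 3 points, and co-artemether is not worse than Lapdap by 3 points. Showing both means rejecting two one-sided hypotheses. With 0.025 on each side, that is the same as the 95% interval for the difference in day-28 failure lying wholly inside −3 to +3 points.

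The label and the method point to something narrower. Non-inferiority is ordinarily a claim in one direction against a named reference, and a Farrington-Manning calculation at 0.025 returns the power to reject one margin. The power is nevertheless claimed for the mutual aim. A reader cannot tell which hypothesis the 80% belongs to.

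At stake is the chance that the trial ends without its stated conclusion. If the 80% is for one direction and the drugs are truly equal, the risk of not establishing the mutual claim is about 40% rather than 20%. The gap widens as the failure rate rises.

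**Working it through.** **Inputs from the protocol (B4).** 1180 randomised; 10% loss; margin 3 points; level 0.025; power at least 80%; Farrington-Manning.

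**Assumptions.** 1:1 allocation; equal true failure rate p in both arms; 0.025 taken as one-sided for each test. p is not stated, so a range is shown.

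**Evaluable children.** 1180 × 0.9 = 1062, or 531 per arm.

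**Formulas.**
- One direction: power = Φ((0.03 − 1.96·s₀)/s₁). Here s₁ = √(2p(1−p)/531), and s₀ is the standard error from the two failure rates fitted under a 3-point difference (restricted maximum likelihood).
- Both directions, equal true rates: power = 2 × (one-direction power) − 1. This holds because, when the rates are equal, failing in both directions at once is practically impossible at these sizes.

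**Worked case, p = 3%.** The restricted rates are 5.1% and 2.1%, so s₀ = 0.0114; s₁ = √(2 × 0.03 × 0.97/531) = 0.01047. Power for one direction = Φ((0.03 − 0.02234)/0.01047) = Φ(0.73) = 77%. Both directions: 2 × 0.7675 − 1 = 54%.

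**Can 1180 be reproduced?** Not uniquely, because p is missing. Two readings fit:
- 80% for one direction at p ≈ 2.7% (about 3.1% with an unpooled variance).
- 80% for both directions at p ≈ 1.9% (about 2.3% unpooled).

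**Power at 531 per arm.** The exact column enumerates the binomial outcomes and applies the Farrington-Manning score test.

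| Failure rate in both arms | Formula: one / both | Exact: one / both |
|---|---|---|
| 2% | 88% / 77% | 90% / 80% |
| 2.5% | 82% / 65% | 84% / 68% |
| 2.7% | 80% / 60% | 82% / 63% |
| 3% | 77% / 54% | 78% / 56% |
| 4% | 67% / 33% | 68% / 35% |
| 5% | 59% / 17% | 59% / 18% |

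Wherever the one-direction power is exactly 80%, the power for both is 2 × 0.80 − 1 = 60%.

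**Where 3% comes from.** 100% − 97% = 3%, from the Thai figure in B1. The same section warns that compliance with the six-dose regimen may be poor when doses are unsupervised, so a lower failure rate cannot be presumed here.

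**For scale.** 80% power for both directions needs 90% in each. By the Farrington-Manning formula with 10% loss, that is about 1552 randomised at 2.7% failure and about 1678 at 3%. For one direction at 3% it is 1274.

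**The case against.** The strongest reply is that the protocol never says the 80% was computed for one direction. Farrington-Manning at 0.025 is also what each of two one-sided tests would use with a 95% interval, and 1180 does give about 80% for both directions if failure is 1.9% to 2.0%. This stands. A reader might infer that the trial's power is 60%; the document does not support that as a flat statement. The 60% holds only if the 80% is one-directional and the true rates are equal. Nor is an arithmetic error shown, since the missing failure rate prevents a unique check of 1180.

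B4 also uses the word non-inferiority, never equivalence, says the size rests mainly, not solely, on the primary endpoint, and gives both the number and the power as minimums. This stands as well: equivalence is the structure of the worded aim, not a named objective. It does not settle which hypothesis the power refers to.

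A reader might also infer that, with no direction fixed, a success in one direction would mean little or would inflate the error rate. Neither follows. The two null hypotheses cannot both be true, so testing both directions leaves at most one opportunity for a false claim. With one drug truly 3 points worse (5% against 2%, or 6% against 3%), it is wrongly declared non-inferior 2.3% and 2.4% of the time at 531 per arm. A one-direction success still excludes a 3-point deficit for that drug.

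Lastly, the decision rule may sit in an analysis plan that is not shown. That could settle the rule for success, but B4 itself attaches the power to a mutual aim, and the power statement has to match the hypothesis there.

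**Conclusion.** The point holds as a mismatch between the claim and its power. B4 claims at least 80% power for a mutual aim without a reference arm, cites a method that gives power for one margin, and leaves open which is meant.

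Its size depends on the failure rate. At 2% or below the claim is met, or nearly so, even on the mutual reading. At 3%, the rate implied by the one day-28 cure figure quoted for a regimen under study, the mutual claim falls 24 to 26 points short of 80% (54–56%), and even the one-direction power is slightly short (77–78%). At 4% the figures are about 67–68% and 33–35%.

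These results assume 1:1 allocation, 531 evaluable per arm and no true difference. The 3% comes from another setting and is used only to locate the range. Supplying a failure rate alone would not resolve the point, because it would not say whether one direction or both must succeed.

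**What to change.** Keep the 1180 children and make the claim and the power agree in B4, in one of two ways:

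- **(a) One direction.** Name the reference arm and the direction before any data are seen, attach the stated power to that hypothesis only, and report the reverse comparison as secondary.
- **(b) Mutual claim.** Define success as the whole 95% interval for the difference in day-28 failure lying within −3 to +3 points, and restate the power as that for both directions.

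In either case, state the assumed failure rate and allocation ratio, and give the power at that rate for the hypothesis chosen.

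The cost is rewriting one paragraph, with no extra patients and no new data. The price is a narrower claim under (a), or, unless failure is expected at about 2% or lower, a less favourable power figure under (b).

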
Lapdap acts in a similar way to SP, by inhibition of the enzyme dihydrofolate reductase (DHFR). Resistance to pyrimethamine is conferred by simple point mutation of the gene for DHFR (Plowe et al, 1996). It is likely that there is a small but constant rate of mutation of this gene during the parasite’s sexual cycle. Only those mutations conferring benefit surviving to predominate. In the presence of selection pressure of antifolate drug, mutations of DHFR which reduce sensitivity to the drugs tend to be selected during the asexual cycle in the human host, and then pass on to the next host via the mosquito vector. Four point mutations are particularly important, at codons 108, 51, 59 and 164. In Africa the DHFR drug resistant phenotype is initiated by mutation at 108, followed by mutations at 51 and 59; the triple mutant 108+51+59 is associated with poor clinical response. All three mutations occur in The Gambia but their prevalence is not known. Lapdap appears effective against some SP-resistant parasites and is likely to exert less selection pressure than SP because of its shorter half-life. It is therefore of interest to examine possible association of these mutations with Lapdap treatment failure and also to measure the frequency and transmissibility of these genotypes after Lapdap treatment.

Co-artemether is a fixed-dose combination that has been shown to be safe and efficacious in supervised trial conditions. Following findings that the 4-dose regimen produced only 76% cure rates by day 28 in Thailand, compared to 97% for the 6-dose regimen, WHO are recommending the 6-dose regimen. Since compliance to this complex regimen may be poor in operational settings it is important to evaluate coartemether when doses are unsupervised. We therefore propose to compare the effectiveness of Lapdap and Co-artemether for treatment of uncomplicated malaria in an operational setting. We will also investigate acceptability of the treatments and compliance, the safety of treatment in G6PD-deficient and normal malaria patients, the effects of treatment on transmissibility of P.falciparum, the cost effectiveness of the two treatments.

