**Study design and methods**

*Study area and study population*

Patients will be recruited from three health centres, Farafenni Maternal and Child Health (MCH) Clinic, which serves the rural town of Farafenni; Njaba Kunda, a mission clinic in a rural village; and Brikama Health Centre, a Government health centre serving a large urban community. Children aged 6 months to 10 years presenting at health centres with a history of illness, who have a fever or recent history of fever, will be screened and those with uncomplicated malaria, a positive blood smear with a parasite density 2000 to 200,000 parasites/μl, monoinfection with *P. falciparum*, and a packed cell volume of >=20%, will be invited to enrol into the study after written informed consent is given

*Treatment and follow-up*

The study patients will be randomised to receive three daily doses of Lapdap, or a six-dose course of co-artemether. Dosages will be determined according to manufacturers’ instructions. The first dose will be given by the mother under direct observation of the dispensing nurse, and subsequent doses will be given at home unsupervised. The parent/carer will be encouraged to bring the child back to clinic if the child’s condition does not improve

The parent/carer will be visited at home a day after the last dose should have been taken (Day 3) in order to check any left over medication, to ask about compliance and adverse reactions and to collect finger prick blood samples for haemoglobin check using Hemocue (portable haemoglobin analyser machine. Haemoglobin results will be entered in lab forms pre-printed with Day 0 haemoglobin results. Patients with severe anaemia (Hb 5 g/dl) or Hb that has fallen by 2g/dl or more from the Day 0 measurement will be promptly referred to the clinic for treatment. Nurses and drivers will be placed on 24-hour emergency duty at the health centres/hospital where the study is sited to handle emergencies. Recruitment will be limited to 5-8 kilometre radius of the study site for quick access to a clinician in the case of an emergency.

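### The claim of at least 80% power with 1180 children states no failure rate; it needs at most about 2.7% failure in each arm, and the protocol's only cure figure for a study regimen gives about 77%

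*Protocol*

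**What the plan says.** Protocol B4, on the size of the study: "We require at least 1180 patients to be randomized, this allows for 10% loss to follow up". The next item, which asks for the sample size calculation, gives the aim as "We wish to demonstrate that the new combinations are at least as good as each other within a margin of 3" per cent and continues: "To have at least 80% power for this, using the method of Farrington and Manning and a significance level of 0.025". Neither item gives an expected failure or cure rate for either drug. Pooling with other countries is mentioned there only for the effect of G6PD deficiency on anaemia.

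The endpoint, in B3 under Study design and methods, is binary: "The primary endpoint will be clinical and parasitological cure by day 28". The same section describes the arms: "The study patients will be randomised to receive three daily doses of Lapdap, or a six-dose course of co-artemether". It gives no allocation ratio. Only the first dose is observed.

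B1 Background has the only day-28 cure figures for either drug: "the 4-dose regimen produced only 76% cure rates by day 28 in Thailand, compared to 97% for the 6-dose regimen". On routine use it says "Since compliance to this complex regimen may be poor in operational settings". The risk and benefit item of the ethics section adds that the effect of poor adherence on efficacy is not known for either regimen.

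**The concern.** For a difference between two proportions, the variance depends on the underlying rate. Margin, alpha, power and method together do not fix a sample size, so 1180 rests on a rate that the reader has to infer. That rate turns out to be very low, slightly better than the supervised result quoted in B1. The trial, however, is run because results outside supervised conditions are uncertain. If failure is even moderately above the implied rate, the chance of showing non-inferiority within 3 points falls quickly, and the trial could end without an answer to its main question while its protocol promises at least 80% power.

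**Working it through.** **Inputs from the protocol.** 1180 randomised, 10% loss, margin 3 percentage points, 80% power, Farrington-Manning, 0.025 (all B4).

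**Assumptions added here.** 0.025 is one-sided, allocation is 1:1, and the two true failure rates are equal (common rate p).

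**Evaluable children.** 1180 × 0.9 = 1062, so 531 per arm.

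**Formula.** Let q1 and q2 be the failure rates fitted under the null hypothesis that they differ by exactly 0.03. Let S0 = √[q1(1−q1) + q2(1−q2)] and S1 = √[2p(1−p)]. Then

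- n per arm = [(1.960·S0 + 0.842·S1) / 0.03]²
- power = Φ[(0.03 − 1.960·S0/√n) / (S1/√n)]

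**The plan's own figure.** It cannot be reproduced directly because p is not given. Solving for p at n = 531 and 80% power gives p = 2.71%. As a check at p = 2.7%: q1 = 0.0485, q2 = 0.0185, S0 = 0.2537, S1 = 0.2292, so n = [(0.4972 + 0.1929)/0.03]² ≈ 530 per arm after rounding up. Then 530/0.9 ≈ 589 per arm, or 1178 in total, against 1180 stated.

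**At the 3% failure implied by the 97% figure.** q1 = 0.0510, q2 = 0.0210, S0 = 0.2628, S1 = 0.2412.

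- Power at 531 per arm: (0.03 − 1.960 × 0.01140)/0.01047 = 0.73, and Φ(0.73) ≈ 77%. Simulating the score test gives 78%.
- Size for 80%: 573 per arm; 573/0.9 ≈ 637, or 1274 in total.

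**Over a range of common failure rates:**

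| Failure rate, both arms | Power with 531 per arm | Total randomised for 80% |
|---|---|---|
| 2% | 88% | 954 |
| 2.7% | 80% | 1178 |
| 3% | 77% | 1274 |
| 4% | 67% | 1604 |
| 5% | 59% | 1932 |
| 10% | 37% | 3528 |

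The rows from 4% upwards are illustrations; the protocol gives no figure for failure under unsupervised dosing.

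**Sensitivity of the 2.7% limit:**

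| Change | Highest failure rate giving 80% power |
|---|---|
| Loss added as 10% of n (536 per arm) | 2.75% |
| No loss at all (590 per arm) | 3.1% |
| Unpooled variance instead of the named method | 3.1% |
| One-sided 0.05 | 3.7% |
| One-sided 0.0125 | 2.0% |
| Non-inferiority required in both directions (unpooled) | 2.3% |

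**The case against.** **No arithmetic error is shown.** This stands. With no rate stated, 1180 cannot be called miscalculated; it is consistent with about 2.7%. The fault is an undisclosed assumption beneath an unqualified power claim.

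**The documented gap is small.** This also stands. At 3% failure the shortfall is about 3 points. The unpooled formula would give about 82%, complete follow-up would give 81%, and 1180 is described as a minimum. But the protocol names Farrington-Manning and plans for the loss, and the unpooled formula still gives only 61% at 5% failure.

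**The 97% is not a planning value.** It comes from another country and one arm, is not cited in B4, and has no counterpart for Lapdap. That limits what can be said about the true power. It also leaves the claimed 80% with no stated support.

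**Equal true rates are an assumption.** If failure were 5% in one arm and 6% in the other, the same formula gives about 80% power to show the better arm non-inferior and about 29% for the worse. The stated aim covers both directions, so this qualifies the 2.7% limit but does not rescue the claim.

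**Stronger readings that the protocol does not support.** A reader might infer that the plan itself predicts higher failure. It does not: it says compliance may be poor and that the effect is not known. A reader might also combine the 97% and 76% figures with a guessed share of children missing doses to obtain an expected failure rate. No such share is given, and a prescribed four-dose course in Thailand is not evidence about missed doses here. Finally, one might conclude that new infections will count as failures. The endpoint sentence is silent on this, MSP1/MSP2 typing to separate recrudescence from reinfection is planned, and a separate analysis plan may settle it.

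**Conclusion.** The concern holds in a limited form. The unqualified statement of at least 80% power is true only if day-28 failure is at most about 2.7% in each arm, given the named method, one-sided 0.025, 1:1 allocation, 10% loss and equal true rates. The protocol does not state or support such a rate. The one relevant figure it contains gives about 77%, a minor shortfall. The shortfall becomes serious from about 4% to 5% failure (67% and 59%). Whether failure will be that high cannot be told from the protocol, but the trial is designed to find out what happens when doses are unsupervised, so its power should not depend silently on a near-perfect cure rate. Pooling across countries does not help, because it is planned only for G6PD deficiency and anaemia.

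**What to change.** In B4:

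1. State the assumed day-28 failure rate for each arm, with its source, and say whether it is genotype-corrected, using the MSP1/MSP2 typing already planned.
2. Replace the unqualified 80% with the power that 1062 evaluable children give at that rate and over a plausible range, for example about 77%, 59% and 37% at 3%, 5% and 10% failure. State the allocation ratio and that 0.025 is one-sided, if those are the intended values.
3. If the sponsor wants 80% at the stated rate, recompute the number to be randomised; at 3% failure it is 1274, which is 94 more children than 1180.
4. Keep the 3% margin unless a different one is justified on clinical grounds before enrolment. Do not choose the margin to fit the sample size.

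Items 1, 2 and 4 cost a rewritten paragraph, with no new data and no more patients; the stated power becomes less favourable. Only item 3 would add recruitment.
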